## Randomization and Stratification

- Johns Hopkins generated a list of randomized numbers in blocks of 20 to insure comparability of men randomized to intervention and control arms, within cohort communities or group of “walk in” participants”.

- A random assignment sheet was placed in an opaque sealed envelope. The envelopes in blocks of 20, were generated by Rakai Health Sciences Program Data management using a computerized list provided by JHU, and were retained securely by the Circumcision Data Management Team.

- After enrollment and consent, men were asked to select an envelope from the block of 20 envelopes being used at that time. The envelope contained the assignment sheet showing the randomization number and random assignment to treatment or control arm. The Enrollment Team then affixed the label with the individual’s study ID number to the sheet. (Form 18).

- The assignment sheet with the study ID# labeled was entered into a data base to record study arm allocation.

- The list of random allocation numbers linked to participants was retained at JHU in locked files, and in password protected computers.

- All randomization envelopes were logged out and in daily. A data base monitored used and unused allocation numbers, and tracked disposition of all envelopes.

- Men were randomized at the enrollment visit. If, participants change their minds and withdrew, or at a subsequent preoperative visit, the surgeon determined that circumcision was contraindicated for medical reasons, the men were considered enrolled and randomized.

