## Analysis Plan

### Primary Endpoint, HIV incidence in Males.

This analysis will be done separately for HIV-negative men enrolled in the Gates and NIH trials, and for the combined population of HIV-negative males enrolled in both trials.

HIV incidence per 100 person-years (PY) will be estimated, assuming seroconversion occurred at the mid-point of each follow up interval. In both arms, time from enrollment will be accumulated up to 24 months of follow up. Person time will discount the postoperative period of sexual abstinence for intervention arm subjects. Baseline samples of subjects who seroconvert during the first follow up interval will be tested by detuned EIA and PCR to detect prevalent infections during the window period, and any suspected prevalent cases will be excluded from incidence analyses.

Exploratory data analysis will examine the populations in the two arms at enrollment to assess baseline comparability. HIV incidence will be determined by strata of covariates such as age, marital status, behaviors (e.g., number of partners, condom use), health status and other variables to identify potential confounders. We will also assess contamination (i.e., cross-over) among men allocated to circumcision who do not receive surgery, and among control subjects who opt to have circumcisions performed from non-Project services.

An intent-to-treat approach will be taken, and all men who enroll will be included, irrespective of whether intervention arm participants ultimately receive circumcision, or whether control arm participants crossover and receive circumcision prior to 24 months follow up. The rationale is that a proportion of enrolled men who initially accept circumcision may change their mind prior to receipt of surgery, and such men are likely to be self-selected. Because circumcision is delayed in the control arm, such self-selection could be differential between randomization groups. Therefore, in the circumcision arm, enrolled men who subsequently refuse circumcision, will be ascribed half the person time from enrollment to scheduled date of circumcision.

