We will assess HIV incidence in enrolled HIV-negative men. The primary analytical model that will be used will be Poisson regression to compare the HIV incidence rates between the two study arms.113 The relative incidence of HIV in the circumcision arm versus the control arm, will be estimated using Poisson regression models with adjustment for individual-level variables found to differ between groups at enrollment, and for potential confounding variables. Potential confounders determined from prior risk analyses will include age, marital status, risk behaviors (i.e, number and nature of partners, condom use and alcohol use), or imbalance of covariates between study arms will be used for adjustment in the primary models. Secondary analyses will include any additional potential confounders identified during exploratory data analysis and will include covariates associated with HIV incidence (p < 0.15), or covariates with an incidence RR > 2.0. Poisson multivariate models will be fit for the whole population and for strata of particular interest (e.g., by age, sexual risk behaviors etc.). Although we are doing an individually randomized trial, the structure and logistics of field work requires that men be randomized within communities. Thus, we will also fit Poisson models with random effect terms for each community, to insure adjustment for clustering in HIV incidence.

We will also assess the associations between selected STDs and STD symptoms and incident HIV infection to determine whether effects of circumcision on HIV incidence may be mediated by STD cofactors. If, as expected from prior analyses, selected STDs and STD symptoms such as GUD are associated with incident HIV, we will assess the circumcision effects on HIV incidence using stratified models or via interaction terms.

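### Allocation was blocked within communities or walk-in groups, but the behaviour and combined-trial models state no term for these strata: harmless for male HIV incidence, a small loss of power for common behaviours

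*Protocol*

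**What the plan says.** **Allocation.** Section 8.7 (and 4.3.4 in the same terms) says that "Johns Hopkins generated a list of randomized numbers in blocks of 20 to insure comparability of men randomized to intervention and control arms", and that this was done "within cohort communities or group of" walk-in participants. Each community and each walk-in group is therefore a randomisation stratum.

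**Primary HIV model.** In section 8.8.1, "The primary analytical model that will be used will be Poisson regression to compare the HIV incidence rates between the two study arms". It is fitted "with adjustment for individual-level variables found to differ between groups at enrollment, and for potential confounding variables". On the choice of covariates, "Potential confounders determined from prior risk analyses will include age, marital status, risk behaviors". Community, walk-in group and trial are not named.

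**Added model.** The same section recognises that allocation took place within communities and for that reason says "we will also fit Poisson models with random effect terms for each community". Walk-in groups are not mentioned. Section 3.1.1 says walk-in men lived in accessible communities, so a community could be assigned to them, but the protocol does not say that it will be.

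**Combined analysis.** Section 8.8.1 plans separate analyses of the two trials and one "for the combined population of HIV-negative males enrolled in both trials", with no trial term stated.

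**Behaviours.** Section 8.8.3 plans adjusted odds ratios from logistic regression, again with no stratum term.

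**The concern.** Blocking within strata removes part of the chance difference between arms. An analysis of a binary outcome that leaves the strata out still counts that variation as noise, so its standard error is somewhat too large for the design. The protocol lets in covariates chosen after looking at baseline imbalance, yet leaves out factors known in advance because the allocation was built on them. The one model that reflects the design covers only part of the strata.

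What is at stake is efficiency, not validity. It matters most for the disinhibition endpoints, where a missed difference would be read as reassurance.

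**Working it through.** **1. The plan's own figures (section 8.2).** Inputs: 1.8/100 py in controls, RR 0.53, two-sided 0.05, power 80%.
- The two-proportion formula with p0 = 0.018, p1 = 0.53 × 0.018 = 0.00954 and continuity correction gives 3,210 py per arm (stated: 3,209).
- 2,500 × 0.85 + 2,500 × 0.85² = 3,931 py (stated: 3,932).
- Two looks at 3,028 and 3,932 py per arm with boundaries 2.303 and 2.017: simulated power 89.3% (stated 89.5%), chance of crossing at the interim 70.0% (stated about 70%), type I error 4.95% (stated 5%).

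These figures make no allowance for strata, and step 2 shows that they need none.

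**2. Male HIV incidence.** The unstratified log rate ratio is log(D1/T1) − log(D0/T0), with SE = √(1/D1 + 1/D0). Stratum counts that are Poisson sum to a Poisson count. With person-time in the same ratio in every stratum, stratum terms cancel, so estimate and SE are the same with or without them. At plan values D0 = 0.018 × 3,932 = 70.8, D1 = 0.53 × 70.8 = 37.5, and SE = √(1/70.8 + 1/37.5) = 0.202.

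Simulation check (assumed: 5,000 men, 50 or 73 strata, blocks of 20, between-stratum CV of incidence 0 to 1.0; 10,000 runs per scenario; Poisson Wald test against a Mantel-Haenszel stratified rate ratio):

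| | Unstratified | Stratified |
|---|---|---|
| Type I error | 4.5-5.2% | 4.5-5.2% |
| Power at RR 0.53 | 88.7-89.8% | 88.6-89.8% |

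The mean rate ratio agreed to three decimals in every scenario.

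**3. Common behaviours.** Section 8.5 gives about 25% with multiple partners and about 46% with recent alcohol use. The share of binary variance lying between strata is ρ = (CV·p)²/[p(1−p)]. Blocking removes this share from the true variance of the arm difference, while the unstratified test still includes it. Approximately:
- actual type I error = 2[1 − Φ(1.96/√(1−ρ))]
- unstratified power, nominally 80% = Φ(0.84/√(1−ρ))
- stratified power = Φ(2.80/√(1−ρ) − 1.96)

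| p | Assumed CV | ρ | Type I error, unstratified | Power, unstratified → stratified |
|---|---|---|---|---|
| 0.25 | 0.3 | 0.075²/0.1875 = 3.0% | 4.7% | 80.4 → 81.2% |
| 0.25 | 0.5 | 0.125²/0.1875 = 8.3% | 4.1% | 81.0 → 83.3% |
| 0.46 | 0.3 | 0.138²/0.2484 = 7.7% | 4.1% | 80.9 → 83.0% |

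Simulation of the unstratified logistic test against a stratified test, with CVs of 0.3 to 0.5, gave type I error of about 3.6-4.6% and a gain of about 1-3 points. A second simulation at p = 0.25 (5,000 men, 50 or 73 strata, 20,000 runs) gave 4.2-4.8% and a gain of 0.8-2.9 points. A CV of 0.5 at p = 0.46 would mean a between-stratum SD of 23 percentage points. It would give a larger loss, but I treat it as outside the plausible range.

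**4. How sparse the strata are.** Section 8.6 expects 69 men per community. Over two years that is 69 × (0.85 + 0.85²) = 108 py, or 54 per arm. Expected HIV events are 54 × 0.018 + 54 × 0.00954 ≈ 1.5 per community. Fixed stratum effects would therefore be a poor choice for HIV.

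**The case against.** Three stronger readings are tempting, and the protocol supports none of them.

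- **That the primary HIV standard error is wrong or too large.** It is not. Step 2 shows that the unstratified Poisson SE is already right, and type I error and power do not move. The variance-share formula in step 3 belongs to binary outcomes and gives no gain for the HIV rate model.
- **That there are two competing HIV results with no rule between them.** Section 8.8.1 names one model as primary and introduces the other as additional. The order is stated.
- **That pooling the trials confounds the result.** Men were allocated within each trial, so trial cannot materially confound arm. The 1.5 and 1.3/100 py in section 8.2 compare men who decline with men who accept VCT, not the two trials. The trial summary in section 1.3 also plans about 500 Gates men who accept VCT. Separate analyses by trial are planned as well.

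It can also be said that the coding of walk-in men is a detail for the statistical analysis plan, and that changing the primary model now would be post hoc, because section 1.3 says the NIH trial has stopped for efficacy and been published. The second argument stands: the primary HIV model should not be reordered. The first stands only in part. The protocol itself lists the adjustment terms and specifies the random effect, and that specification does not match its own randomisation strata.

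**Conclusion.** The mismatch between design and analysis is real and minor. The primary result on male HIV incidence is unaffected in estimate, standard error and power. For common binary behaviours, leaving out the strata makes the test mildly conservative and costs about 1-3 points of power. That size rests on assumed between-stratum CVs of 0.3 to 0.5 and on 50 or 73 strata. The protocol gives neither a CV nor a number of strata, and with little variation between strata the loss disappears. The missing trial term in the combined analysis is a matter of good form, with no material bias expected.

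**What to change.** - In the behaviour and STD models, include the randomisation stratum (community or walk-in group), as a random effect or through a stratified analysis, because the strata are sparse.
- In the planned random-effects Poisson model for HIV, give walk-in groups their own terms alongside communities, and state how walk-in men are coded.
- In the combined NIH and Gates analysis, stratify by trial.
- Leave the primary HIV model where it is.

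The cost is a few sentences and some extra model fitting. No new data are needed, provided the allocation records identify each man's stratum.

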### Female HIV Acquisition

We propose an intent-to-treat analysis . The unit of analysis is women in relationships with HIV-positive male partners. Although the male’s circumcision status can be ascertained by interview with the female partner, the male’s HIV status can only be determined by linking couples from within the RCSS. This will be done at the conclusion of follow up. The linkage will allow identification of men enrolled in the circumcision trials, determine their randomization arm and their HIV status, and provide an objective measure of circumcision status as well as the timing of the circumcision.

We will determine male-to-female transmission (female HIV incidence per 100 py) in the circumcision arm relative to control using multivariate Poisson regression as described for male HIV acquisition in 8.9.a above.

Data are also collected on the frequency of intercourse, so in addition, we will estimate the probability of HIV infection per coital act among circumcised and non-circumcised men using published methods.20,116 The probability of transmission in the ith couple (Pi) can be written as 1- (1-) n i, where ni is the number of acts during the follow up period, and the infectivity () is the probability of transmission per act.116 Allowing the infectivity to depend on covariates through a complementary log-log link, leads to the regression model [log -log (1-P)] = log ni + b0 + b1X1 where b1 and X1 are vectors of regression coefficients andcovariates, respectively. This model will be fit using statistical methods for generalized linear models, specifically binomial regression with a complementary log-log link and offset term log ni (SAS Institute Inc., Cary, NC.). The comparisons will again be between circumcision arm and control. We have shown that the probability of male-to-female HIV transmission per coital act is 0.0004 if the malepartner was circumcised and 0.0015 if the male was uncircumcised (RR = 0.27, unpublished).

We observed no seroconversions among women whose circumcised male partner’s viral load was below 50,000 copies per mL, whereas in uncircumcised men with viral loads <50,000 cps/ml, the female incidence rate was 9.6/100 py. In our couples study, 87.1 % of infected men in discordant relationships had viral loads < 50,000 copies per mL. Therefore, we examine the efficacy of male circumcision in prevention of female HIV acquisition, by strata of male HIV-positive partner viral loads. Since this is an *a priori* hypothesis, based on observational data, such subgroup analysis is justified.

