## Female HIV Acquisition*.*

Information on women will be derived from the RCSS surveillance surveys, and women are not enrolled in the male circumcision trials. Female HIV acquisition associated with the male partner’s circumcision status will be assessed among HIV-negative women in relationships with HIV-positive men. Please note, we do not enroll HIV-discordant couples; the men are individually enrolled in the circumcision trials and the women individually enrolled in the RCSS. Couples linkage will only be done retrospectively after completion of the trials, although promotion of couples VCT will be ongoing throughout the study. The information on male partner circumcision and HIV status will be derived from this retrospective linkage.

Our observational data in HIV-discordant couples found a male-to-female transmission incidence of 5.2/100 py if the male was circumcised and 13.2/100py if the male was uncircumcised (RR = 0.39). (Please note, we strongly promote condoms and couples counseling, but acceptance of these services within married couples is low). We estimate sample sizes required to detect an efficacy of this magnitude, with  = 0.05 and 1- = 0.80. The person years accrued for female exposure in discordant couples with an HIV+ male partner can be estimated from the number of prevalent and incident discordant couples with HIV+ men, as follows:

***i.*** *Person years contributed by prevalent HIV+positive men in discordant relationships with HIV- negative women:* We estimate that 500 HIV positive males per arm will accept enrollment . From prior data, 80% of men can be linked to a female partner and 55% of prevalent HIVpositive men have HIV-negative female partners. Thus we expect 220 HIV prevalent males in a discordant relationship (i.e., 500 x 0.8 x 0.55). Assuming

85% annual follow up, we estimate that 220 HIV-discordant, male HIV+/female HIV- couples, will provide 186 py in the 1st follow up year and 158 py in the 2nd follow up year, yielding a total of 344 person years in exposed, initially HIV- women. With 344 py per arm, will have 85% power to detect a RR = 0.39. Assuming 7.5% contamination, the sample size is sufficient to detect a RR* of 0.41 with 80% power.

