## Behavioral disinhibition:

These estimates are based on the total populations of HIV- men enrolled in the Gates and NIH trials

From prior data we expect ~ 25% of men to have multiple sex partners, ~ 17.0% to use condoms inconsistently, ~ 5.0% to consistently use condoms, ~ 46.0% report alcohol consumption in the previous 7 days and ~42% report alcohol consumption with sex. These behaviors have been shown to be significantly associated with HIV risk in the Rakai population. Assuming these rates pertain in the control arm, we will have 80% power to detect the following markers of behavioral disinhibition in the intervention arm: a) an increase in multiple sex partners to 30%, b) a reduction of inconsistent condom use to 13.2%, and c) a reduction in consistent condom use to 3% (i.e., an overall reduction in condom use of - 5.8%), and d) and an increase in alcohol use within the past 7 days to 50.4%, or of alcohol consumption with sex to 46.4%.

We will also assess behaviors among the ~1000 men who decline VCT, compared to the men who accept VCT, to determine whether VCT acceptance is associated with lower risk behaviors.

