## Brief description of the cohort surveillance

This is an open cohort that has conducted annual surveys of persons resident in the cohort communities who consent to cohort participation. The cohort consent forms are appended, and these have been approved by all IRBs.

Consenting individuals complete an interview at enrollment and at each follow up to ascertain sociodemographic characteristics, behaviors (e.g., numbers and types of sexual partners, sexual networks, condom use, alcohol use sex, coercive sex and domestic violence), genital hygiene, health status (symptomatology suggestive of STDs or AIDS, use of health care services), use of VCT and family planning. Partner information is obtained via questions on sexual networks (up to 4 partners within the past year) and by linkage information that allows identification of marital or consensual partners enrolled in RCCS.

Serum samples are obtained for serology (HIV and syphilis) and aliquots are stored for future testing. Women are asked to provide self-collected vaginal swabs for detection of trichomonas, BV, HPV, gonorrhea and chlamydia stored for future testing. Persons with symptomatic GUD are asked for an ulcer swab for Multiplex PCR detection of infections such as HSV-2, syphilis and chancroid, and stored for future testing.

Please note, with the exception of HIV and syphilis serology, none of these tests can be run in real time and used for therapeutic purposes.

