### Ethical Dilemmas that Arise if Women were Excluded:

OHRP guidelines require the “inclusion of both women and men in research, both to insure that they receive appropriate share of benefits of research, and that they do not bear disproportionate burden”.146 Thus, inclusion of women in this study is consistent with Federal policies, since could benefit from reduced HIV and STD risks. The Rakai cohort has always included resident consenting adults of both sexes, and if women were excluded from the trial, the long established community relationships and bonds of trust could be compromised. We believe that exclusion of women is not a viable option in the context of Rakai population-based studies, and that the trial cannot be conducted if women are excluded. The ethical rationale for inclusion of women is as follows:

**1) *Potential Stigmatization:*** The male-to-female HIV transmission end point will be assessed in couples where the male is HIV+. However, we could not selectively identify and follow up such couples because it would highly stigmatizing. We will maintain surveillance of consenting female partners (wives and permanent consensual partners) of men enrolled in the trial, but we will not enroll discordant couples *per se*. Our rationale is that adult participants of both sexes provide individual informed consent on enrollment into the cohort, and they are free to accept VCT by individual choice. Free, confidential VCT is offered to individuals and couples, and all participants are strongly encouraged to share HIV results with their partners, and to receive couples counseling. However, specific enrollment of HIV-discordant couples, ethically requires that both parties accept VCT, and in our experience, such a requirement would be a disincentive both for acceptance of VCT and for enrollment. Our VCT program is successful because it emphasizes personal choice and is not coercive or restrictive. This is, in our view, the only ethically defensible approach to community-based research and service, and is concordant with Ugandan Ministry of Health policy.

**2)*Omission of derivative benefits to women and public health rationale for circumcision:*** Exclusion of female partners of enrolled men would preclude assessment of potential derivative benefits for women, and this would weaken the public health rationale for future introduction of circumcision programs.

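### The female HIV models name no term for women who share a randomised man; if men have two or more linked HIV-negative women, the standard errors would be slightly too small

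*Protocol*

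**What the plan says.** Allocation is by man: each man draws his own envelope (4.3.4 and 8.7). Section 8.4 says that "the men are individually enrolled in the circumcision trials and the women individually enrolled in the RCSS", with couples linked afterwards. The female analysis in 8.8.2 compares the men's arms, but "The unit of analysis is women in relationships with HIV-positive male partners".

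Female incidence is compared "in the circumcision arm relative to control using multivariate Poisson regression as described for male HIV acquisition in 8.9.a above". No such subsection exists; the male analysis is 8.8.1. That section specifies Poisson regression and then one clustering device, as an additional model: "Thus, we will also fit Poisson models with random effect terms for each community, to insure adjustment for clustering in HIV incidence". The second female model in 8.8.2 is a binomial regression per coital act with complementary log-log link, indexed by couple. Neither female model has a term, a robust variance or a selection rule for women who share a man.

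On how many women may belong to one man:
- Section 10.8.2: "We will maintain surveillance of consenting female partners (wives and permanent consensual partners) of men enrolled in the trial".
- Section 9.4: men receive a referral slip for their wives or partners.
- Section 9.3: "Partner information is obtained via questions on sexual networks (up to 4 partners within the past year) and by linkage information" on partners enrolled in the cohort.
- Section 8.4: the sample size turns 220 men per arm into 220 couples per arm.

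**The concern.** In the male analysis the randomised person is the analysed person, so no within-man term is needed. That stops being true when the model is applied to women. Two women linked to one man share his arm, and they share causes of infection that the protocol itself treats as important. Sections 8.4 and 8.8.2 make the man's viral load central to transmission, and 1.1 and 10.7.3 relate the interim excess in female infections to sex before certified wound healing. Positive correlation within a man is therefore plausible. A community random effect picks up shared local incidence, not a shared infecting partner.

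Efficacy in women and safety of partners are both in the primary objectives (2.1), and the monitoring board was weighing a non-significant excess of female infections. Positive correlation that is left out makes intervals too narrow, whether the result points to benefit or to harm.

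**Working it through.** **The plan's own figure (8.4).** 500 × 0.80 × 0.55 = 220 couples per arm. Person-years: 220 × 0.85 + 220 × 0.85² = 187 + 159 = 346, against 344 stated, so the count reproduces. It rests on one woman per man. (The stated 85% power does not reproduce at 344 person-years: standard formulas at two-sided 0.05 give 92 to 96%. That is a separate matter.)

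**Inputs that are missing.** The share *f* of men with two linked HIV-negative women and the within-man correlation (ICC) are not given. The nearest figure is in 8.5: "From prior data we expect ~ 25% of men to have multiple sex partners". It refers to HIV-negative men and to any partner, so *f* = 25% is a generous ceiling. Applying the linkage and discordance fractions of 8.4 to the second woman (an assumption) gives 0.25 × 0.80 × 0.55 = 11%.

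**Design effect.** With *m* women per man, DE = 1 + (Σm²/Σm − 1) × ICC. If a share *f* of men has two women and the rest one, Σm²/Σm − 1 = (1 + 3f)/(1 + f) − 1 = 2f/(1 + f). The true standard error is √DE times the model's, and the type I error is 2 × [1 − Φ(1.96/√DE)].

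| f | ICC | DE | SE ratio | Type I error |
|---|---|---|---|---|
| 0 | any | 1.000 | 1.000 | 5.0% |
| 5% | 0.1 | 1.010 | 1.005 | 5.1% |
| 10% | 0.2 | 1.036 | 1.018 | 5.4% |
| 25% | 0.1 | 1.040 | 1.020 | 5.5% |
| 25% | 0.2 | 1.080 | 1.039 | 5.9% |
| 25% | 1 (ceiling) | 1.400 | 1.183 | 9.8% |

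Example: for f = 25% and ICC 0.2, 2 × 0.25/1.25 = 0.40, so DE = 1 + 0.40 × 0.2 = 1.08.

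**Simulation.** 220 men per arm, 13.2 per 100 person-years in both arms, 85% annual follow-up, gamma-distributed infectiousness per man with variance 1 to 4:

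| Men with two linked women | Type I error, model SE |
|---|---|
| none | 4.7–4.9% |
| 11% | 4.9–5.6% |
| 25% | 5.7–6.8% |

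Standard errors clustered on the man keep the type I error at 4.5 to 5.2% throughout. For the 11 and 25% rows, the true standard error is about 1 to 9% above the model's. Not all of that is clustering: with one woman per man, where no clustering is possible, simulation still shows an excess of up to 2 to 3%, which should not be counted against the plan.

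**Power.** At 344 person-years, f = 25% and ICC 0.2 lower the power by about 2 points (91.9 to 89.9% by the log rate-ratio test).

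**The case against.** The strongest reply is that the protocol never says that women are independent or that model-based standard errors will be used. A robust variance is a detail often left to the analysis plan, which is not at hand. The planning and the per-act model are by couple, and with one woman per man nothing is wrong. Stratifying by viral load should also absorb part of what women linked to one man share.

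Much of this stands, and it limits the size of the point. It does not remove it. The protocol does fix a clustering structure, by community, and so leaves out the unit that was randomised. No rule restricts the analysis to one woman per man. Viral-load strata do not cover wound healing or resumption of sex.

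Stronger readings are tempting but not supported:
- A reader might infer that the standard errors *are* too small. That needs men with two or more linked HIV-negative women, and the protocol does not say how many there are.
- A reader might take the limit of four partners in 9.3 as women per man. It is the limit of an interview question. The women analysed must also be enrolled in the cohort, linked and HIV-negative.
- A reader might assume 1.4 women per man. With at most two each, that means 40% of men with two linked HIV-negative women, which exceeds even the 25% with several partners of any kind. It is an extreme case, not a planning value.

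**Conclusion.** The structural gap is in the text: allocation by man, analysis by woman, several women per man permitted, and community as the only cluster term. The consequence is conditional and probably small. Under the assumed values (11 to 25% of men with two linked women, frailty variance 1 to 4), the true standard error is about 1 to 9% larger than the model's and the type I error is about 5 to 7%. With one linked woman per man there is no error. Nothing in the protocol suggests that this alone would reverse a conclusion on efficacy or harm. Confidence is high in the structure and low to moderate in the size. It is a minor point and a nearly free improvement.

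**What to change.** In 8.8.2, state that both female models, the Poisson model and the per-act complementary log-log model, take the index man as the cluster. A cluster-robust or GEE variance would serve, or a random effect per man. The community random-effect model can stay as an additional analysis. Report the number of linked HIV-negative women per man by arm, so that the reader can see whether the issue arises at all.

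The cost is one option in the model code and slightly wider intervals. No new data are needed: the linkage in 8.8.2 already identifies each woman's partner and his arm.
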